**Minimally Invasive Surgeries for Hypertensive Intracerebral Hemorrhage (MISICH): Study Protocol**

**Department of Neurosurgery**

**Chinese PLA General Hospital**

**Background**

Hypertensive intracerebral hemorrhage (HICH) is a crucially important neurological emergency characterized by high fatality and disability rate. HICH accounts for about 70% of all intracerebral hemorrhage (ICH) cases. It affects about 4 million people worldwide each year and the median mortality at 1 month is 40%. Many survivors remain severely disabled, and only 12% of the survivors could live independently with minor handicap after 6 months, posing a huge burden on the society and families.

Theoretically, surgery has the potential to improve neurological recovery after ICH since early removal of the hematoma might reduce nervous tissue damage, possibly by relieving local ischemia or removal of noxious chemicals. However, the effectiveness of surgery (mainly refers to craniotomy) in the treatment of ICH remains controversial. Several prospective randomized controlled trials (RCTs) have been undertaken during the past 4 decades, but results of most individual trials failed to demonstrate improvement in outcome in surgically treated patients. Results of the STICH trial indicates that patients with spontaneous supratentorial ICH in neurosurgical units show no overall benefit from early surgery when compared with initial conservative treatment. The STICH II trial, a study based on subgroup analysis of the STICH trial, confirms that early surgery does not increase the rate of death or disability at 6 months and might have a small but clinically significant survival advantage for patients with spontaneous superficial ICH.

Minimally invasive surgery generally refers to the concept of creating minimal trauma to normal brain tissue during the process of removing hematoma. This stands in distinction from the open craniotomy in which a large bone flap is created, the brain is exposed, retracted, and manipulated to inspect the site of bleeding and suction blood from multiple areas. Two main types of minimally invasive surgery have been attempted for hematoma removal: endoscopic evacuation and stereotactic aspiration. In endoscopic evacuation, a small boneflap is created, and an endoscope is inserted through normal brain tissue into the hematoma with the help of an introducer. Suction and irrigation are applied to remove the hematoma. Auer reported the first randomized trial of endoscopic-guided hemorrhage evacuation with a sample size of 100. Results indicated that endoscopic surgical evacuation offers promise to maximize hematoma evacuation while minimizing damage to normal tissue. Stereotactic aspiration involves using image guidance to place a catheter into the main body of the hematoma and aspirate blood. A catheter is left in the body of the hematoma, and during the course of several days, repeated small doses of thrombolytic agents is instilled via the catheter into the brain to clear the left hematoma slowly. Recently, several studies exploring the efficacy of minimally invasive surgery compared with craniotomy or medical treatment have been carried out, but none of them provided sufficient evidence regarding the choice of treatment. Until now, no results of largescale RCTs comparing the efficacy of endoscopic evacuation, stereotactic aspiration and craniotomy in patients with ICH has been reported. Here we designed a multicenter, randomized, controlled trial to investigate whether minimally invasive hematoma evacuation with endoscopic or stereotactic aspiration will improve functional outcome in patients with supratentorial ICH compared with small boneflap craniotomy.

**Methods/design**

**Objectives**

This trial primarily aims to investigate whether and to what extent endoscopic evacuation and stereotactic aspiration could improve the outcome of supratentorial HICH compared with small boneflap craniotomy. This trial will also help to better define the indications for different surgical methods and help to determine the best surgical method for treatment of supratentorial HICH. Another objective is to evaluate the separate effects of different surgical treatments on patients’ independency and activities of daily living.

**Study design**

This is a multicenter, randomized, controlled, open-label, sequentially designed non-profit study (ClinicalTrials.gov ID: NCT02811614) involving 16 neurosurgical centers. Patients with newly diagnosed supratentorial HICH according with our inclusion criteria will be enrolled in this study. A follow-up period of 6 months will be sufficient enough to show outcome and prognosis of surgical treatment. A flowchart of this study is shown in Figure 1.

[figure not shown]

Figure 1 Flow chart of the study design

The trial will be conducted in the departments of neurosurgery at 16 Chinese hospitals: (1) Chinese PLA General Hospital, Beijing; (2) Jingzhou Central Hospital, Hubei province; (3) Wuhan No.1 Hospital, Hubei province; (4) Jinzhou Central Hospital, Liaoning province; (5) Yichang Central People’s Hospital, Hubei province; (6) Hainan Hospital of Chinese PLA General Hospital, Hainan province; (7) Liaoning Thrombus Hospital, Liaoning province; (8) Jiangmen Central Hospital, Guangdong province; (9) People’s Hospital of Sanshui District. Foshan, Guangdong province; (10) Minzu Hospital of Guangxi Medical University, Guangxi province; (11) The Second Hospital of Jilin University, Jilin province; (12) Jilin Province People’s Hospital, Jilin province; (13) Siping Central People’s Hospital, Jilin province; (14) Tangdu Hospital of Air Force Military Medical University, Shanxi province; (15) The Third Affiliated Hospital of Inner Mongolia Medical University, Inner Mongolia; (16) The First Affiliated Hospital of Xinjiang Medical University, Xinjiang province. All neurosurgeons taking part in the MISICH study have been trained by an annually held national continuing education program by Chinese PLA General Hospital about endoscopic evacuation, stereotactic aspiration, and small boneflap craniotomy. These three surgical techniques have been routinely used in all centers prior to the start of trial.

**Eligibility criteria**

***Inclusion criteria***

1. Men and women aged 18-80 years old

2. Present with supratentorial HICH confirmed by brain computed tomography (CT) scan, hematoma volume ≥25mL

3. Glasgow Coma Scale (GCS) score ≥5

4. Patients are admitted to the above-mentioned hospitals within 24 hours of ictus

5. Patients or their dependents (when patients in coma) provide written consent.

***Exclusion criteria***

1. The hemorrhage is caused by cerebral tumor, coagulopathy, aneurysm or arteriovenous malformation

2. With concurrent head injury or history of head injury

3. There are multiple hemorrhagic lesions

4. Have severe dementia or disability

5. Patients already have indications of terminal brain hernia

6. Patients with concomitant diseases that will affect their life expectancy

7. Hematoma mainly located in ventricular system

8. Pregnant woman.

**Sample size and randomization**

***Sample size***

It was reported that the rate of unfavorable outcome of patients receiving craniotomy with a supratentorial hematoma volume >30 ml was 49% to 67% and minimally invasive surgeries might decrease the rate of unfavorable outcome by about 8% to 22% compared with craniotomy. Our recent retrospective study showed that endoscopic surgery lowered the risk of unfavorable outcome in patients with supratentorial HICH by nearly 28% in comparison with craniotomy. We assume that the endoscopic surgery and stereotactic aspiration could reduce the risk of unfavorable outcome from 33% to 21%. A sample size of 720 (240 in each group) would be required to show a 12% benefit from minimally invasive surgery with 90% power and a type I error probability of .05 with a 10% dropout rate taken into consideration.

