**Outcomes measurements**

The primary outcome of this study is the degree of disability estimated using the modified Rankin Scale (mRS) 6 months after ictus. An unfavorable outcome is defined as death or dependency with a mRS of 3-6. Living patients’ independence in activities of daily lives and quality of life will be a highlight of this study. We will also measure patients’ quality of life and their performance in activities of daily living using the Barthel Index at 6-months follow-up. Secondary outcomes also include: hematoma clearance rate evaluated at 72h after surgery, operation time, intraoperative blood loss, postoperative GCS score 7 days after surgery, rebleeding rate, days of NICU stay, intracranial infection rate during hospitalization, 1 month mortality, 3 months mortality, hospitalization expenses, and Barthel Index at 6 months.

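### The 33% craniotomy rate used for planning is not reconciled with the 49–67% cited beside it; at the cited rates, 720 patients do not give 90% power for an absolute 12-point benefit.

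*Protocol*

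**What the plan says.** All the planning figures stand in one paragraph, Protocol, Sample size.

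- **Evidence on the control rate:** "the rate of unfavorable outcome of patients receiving craniotomy with a supratentorial hematoma volume >30 ml was 49% to 67"%.
- **Evidence on the effect:** "minimally invasive surgeries might decrease the rate of unfavorable outcome by about 8% to 22% compared with craniotomy", and, from the sponsor's own retrospective study, "endoscopic surgery lowered the risk of unfavorable outcome in patients with supratentorial HICH by nearly 28% in comparison with craniotomy". Neither sentence says whether the reduction is absolute or relative.
- **Planning assumption:** "We assume that the endoscopic surgery and stereotactic aspiration could reduce the risk of unfavorable outcome from 33% to 21"%. No source or reason is given for the 33%.
- **Resulting claim:** 720 patients, 240 per group, give 90% power for a 12% benefit at a type I error of .05, allowing for 10% dropout.

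Elsewhere, the Inclusion criteria admit hematomas of 25 mL or more. Outcomes measurements sets the endpoint: "An unfavorable outcome is defined as death or dependency with a mRS of 3-6". Statistical analysis specifies a chi-squared test at a two-sided 5% level and does not say which of the three groups are compared.

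**The concern.** The planned control rate lies 16 points below the bottom of the cited range (49 − 33) and 34 points below the top (67 − 33). The paragraph offers nothing to bridge the gap. The one population difference it shows, above 30 ml against 25 mL or more, is small, and the protocol does not present it as the explanation.

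The control rate matters because the variance of a proportion is largest near 50%. A fixed absolute difference of 12 points is therefore harder to detect from a control rate of 49–67% than from 33%. If the cited range is the better guide and the effect is an absolute 12 points, the trial is less sensitive than stated, and a non-significant result could be over-read as evidence of no benefit.

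**Working it through.** **Inputs.** From Sample size: 240 per group, 10% dropout, control 33%, treated 21%, cited control range 49–67%, cited benefit 8–22%. From Statistical analysis: two-sided 0.05. Evaluable per arm: 240 × 0.90 = 216. The 58% used below is the midpoint of 49–67%.

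**Formula.** For control rate p1 (n1 patients), treated rate p2 (n2 patients), difference Δ and weighted mean rate p̄:

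- s0 = √[p̄(1 − p̄)(1/n1 + 1/n2)]
- s1 = √[p1(1 − p1)/n1 + p2(1 − p2)/n2]
- power = Φ[(Δ − 1.96·s0)/s1]

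**Step 1: the plan's own figure.**

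- *Each arm against craniotomy (216 v 216), 33% v 21%.* p̄ = 0.27, s0 = 0.0427, s1 = 0.0423. (0.12 − 1.96 × 0.0427)/0.0423 = 0.857, so power is 80.4%. For 90% power this comparison needs 286 evaluable per arm; 286/0.9 gives 318 enrolled, or 954 in all.
- *Both minimally invasive arms pooled (216 v 432).* p̄ = 0.25, s0 = 0.0361, s1 = 0.0375. (0.12 − 1.96 × 0.0361)/0.0375 = 1.31, so power is 90.5%. For 90% power this needs 212 per arm, 636 evaluable and 707 enrolled, which is close to 720.
- *Three-group chi-squared test (2 df, noncentral).* Power is 85.5%.

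Of these three readings, only the pooled one supports 90% at 720 with the stated inputs.

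**Step 2: keep 12 absolute points and move the control rate.** Worked example, 49% v 37% pairwise: p̄ = 0.43, s0 = 0.0476, s1 = 0.0473. (0.12 − 1.96 × 0.0476)/0.0473 = 0.563, so power is 71.3%.

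| Control → treated | Each arm v craniotomy | Three-group test | Pooled v craniotomy |
|---|---|---|---|
| 33% → 21% | 80.4% | 85.5% | 90.5% |
| 49% → 37% | 71.3% | 74.9% | 83.2% |
| 58% → 46% | 70.5% | 73.4% | 82.4% |
| 67% → 55% | 72.6% | 74.9% | 84.0% |

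The pairwise minimum is 70.5%, at a control rate of about 56%. Pairwise power stays below its 33% value for any control rate between 33% and 79%, so the direction does not depend on where in the cited range the true rate falls.

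**Step 3: change the effect (pairwise, 216 per arm).** The planned relative risk is 0.21/0.33 = 0.636. The midpoint of 8–22 is (8 + 22)/2 = 15.

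| Effect | Power for control rates 49–67% |
|---|---|
| 8 points absolute | 38.5–40.6% |
| 12 points absolute | 70.5–72.6% |
| 15 points absolute | 88–89% |
| 22 points absolute | over 99% |
| 28% read as relative | 83% at 49%, 98% at 67% |
| Relative risk 0.636 (18 to 24 points) | 97% at 49%, over 99% at 67% |

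The scale and size of the effect therefore move power far more than the position of the control rate within 49–67%.

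**The case against.** The strongest reply is that the loss is conditional. It requires the effect to stay at 12 absolute points when the control rate rises. If the relative risk is the more stable quantity, a higher control rate gives a larger difference and more power than planned. An absolute 22 points, the top of the cited benefit if read as absolute, would exceed 99%. This stands, and it limits the point to the absolute reading. It does not remove it: 33 − 21 = 12, so the plan's 12% is an absolute difference (as a relative reduction it would be 12/33 = 36%), and the 90% claim is attached to that figure.

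A second reply is that the cited 49–67% may not carry over. It refers to hematomas above 30 ml, and the protocol does not give the cited reports' eligibility, endpoint definition or time point. The trial also excludes terminal hernia, multiple lesions, mainly ventricular hematoma and life-limiting disease. This too stands: the true control rate is unknown, and 33% could be right. The protocol does not make that argument, however, and it cites no other rate after craniotomy.

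Three stronger readings are tempting, and the document does not support them.

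- *Power was already short of 90% and is now lower still.* This holds pairwise and for the three-group test. It fails for the pooled comparison, which starts at 90.5%. The words about a benefit from minimally invasive surgery leave pooling open, although Statistical analysis does not state it.
- *Favorable and unfavorable rates were swapped, since 33 = 100 − 67.* Relabelling both rates makes unfavorable outcome go from 67% to 79%, so that minimally invasive surgery would be worse, against the paragraph's stated reduction. Power would not change either: 67% v 79% also gives 80.4%.
- *The Background figures refute 33%.* The 40% one-month mortality and the statement that "only 12% of the survivors could live independently with minor handicap after 6 months" describe the disease in general, not selected patients who undergo surgery. Combining them mixes two time points, and minor handicap is not equated there with the trial's mRS cut.

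**Conclusion.** The point holds in conditional form. The 33% control rate is unexplained and lies outside the only craniotomy range the protocol cites. Given an absolute 12-point benefit, a control rate of 49–67%, 216 evaluable patients per arm and two-sided 0.05 with no multiplicity adjustment, power is about 71–73% pairwise, 73–75% for the three-group test and 82–84% pooled. The stated 90% is not delivered on any of these readings.

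The documents do not show that 33% is wrong or that the trial is underpowered whatever the effect. They show that the 90% claim rests on a rate the protocol neither sources nor squares with its own evidence, and that the unstated effect scale decides whether power is near 70% or above 96%.

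**What to change.** Revise the Sample size text as follows.

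1. Name the comparison that is powered: each arm against craniotomy, the three-group test, or the minimally invasive arms pooled.
2. State for each of the 8–22%, the 28% and the 12% whether it is absolute or relative.
3. Either base the 90% claim on the cited 49–67%, with the effect size that this requires, or give the source that supports 33% for this population and the mRS 3–6 endpoint.
4. Add a four-row table of power at n=720 for control rates of 33%, 49%, 58% and 67%, for the named comparison.

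The cost is a text change, with no added patients and no change to conduct. The stated power may become less favorable. If the sponsor instead chose to keep 90% pairwise power for 12 absolute points, enrollment with 10% dropout would be 396 per group (1,188) at a 49% control rate, 404 (1,212) at 56% and 385 (1,155) at 67%. These figures show the size of the gap; they are not the change proposed here.

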***Randomization***

To minimize selection bias and accidental bias, Patients were randomly allocated to endoscopic evacuation group, aspiration group, or small boneflap craniotomy group in 1:1:1 ratio using a central randomization system based on computer-generated number sequence after a written informed consent was signed. Neither the neurosurgeons nor the patients could know the grouping beforehand. Randomization must take place within 24 hours of ictus and patients will be operated on within 12 hours of randomization. During the randomization process the neurosurgeon is informed of the treatment group the patient is allocated to and should record this. Best medical treatment must begin as soon as possible and continue throughout follow-up in all patients.

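### No stratification by centre or prognosis is stated for a 16-hospital comparison of three operations, and the primary test ignores centre, which costs some precision

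*Protocol*

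**What the plan says.** The Protocol's Randomization section gives the purpose and the three arms: "To minimize selection bias and accidental bias, Patients were randomly allocated to endoscopic evacuation group, aspiration group, or small boneflap craniotomy group". It then gives the method: "in 1:1:1 ratio using a central randomization system based on computer-generated number sequence after a written informed consent was signed". On concealment it says "Neither the neurosurgeons nor the patients could know the grouping beforehand". The section also covers timing, but names no stratum, block or minimisation factor. It does not describe the list as single or unstratified either.

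The Study design section describes a trial "involving 16 neurosurgical centers". On experience it says "All neurosurgeons taking part in the MISICH study have been trained by an annually held national continuing education program", covering all three operations, and adds "These three surgical techniques have been routinely used in all centers prior to the start of trial". The Sample size section says "A sample size of 720 (240 in each group) would be required".

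The Statistical analysis section makes an unadjusted chi-squared test of favourable against unfavourable 6-month outcome the primary analysis. A logistic regression is also planned, with age, sex, hematoma volume, preoperative GCS, operation and intracranial infection as terms. Neither centre nor surgeon is among them.

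**The concern.** The result of an operation can depend on where it is done, through local intensive care, equipment and follow-up. With 16 hospitals, a list that is not balanced within centre lets the mix of operations vary from one hospital to the next. The Randomization section sets out to limit accidental bias as well as selection bias. Central concealment deals with selection bias. Beyond plain randomisation, nothing stated limits chance imbalance over centres or prognosis.

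Centre and GCS could be handled in the analysis instead, but the primary test uses neither. Any outcome variation that they explain therefore stays in the error of the main comparison. What is at stake is the precision and credibility of a comparison meant to identify the best operation. The validity of the test is not at stake.

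**Working it through.** **1. The plan's own figure.** Inputs from the Sample size section are 33% v 21%, 90% power, type I error 0.05 and 10% dropout. The Statistical analysis section makes the test two-sided. With r = size of comparison group / size of craniotomy group and pooled proportion p̄:

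n = [z₀.₉₇₅ √((1+1/r) p̄(1−p̄)) + z₀.₉₀ √(p₁(1−p₁) + p₂(1−p₂)/r)]² / (p₁−p₂)²

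- Both minimally invasive arms pooled against craniotomy (r = 2, p̄ = 0.25): n = (1.039 + 0.707)² / 0.0144 = 212 per arm. 212/0.9 gives 236, and 3 × 236 = 708, close to 720.
- One minimally invasive arm against craniotomy (r = 1, p̄ = 0.27): n = (1.231 + 0.797)² / 0.0144 = 286 per arm. 286/0.9 gives 318, and 3 × 318 = 954.

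So 720 is reproduced for the pooled comparison. With 240 × 0.9 = 216 evaluable per arm, one pairwise comparison has about 80% power. That is the base for step 4. Whether 720 is enough is a separate matter.

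**2. Spread over centres if the list is unstratified.** 720/16 = 45 patients per centre if sizes are equal. This is an assumption, because the Protocol gives no centre sizes.

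- Simple 1:1:1 allocation, 200,000 simulated draws: in a centre of 45, the chance that the largest arm is at least twice the smallest is 0.18. Expected number of such centres: 16 × 0.18 = 2.9. Chance of at least one: 1 − 0.82¹⁶ = 96%.
- A list fixed at exactly 240 per arm but not stratified by centre: about 2.6 such centres, and a 93% chance of at least one. The result does not depend on assuming simple randomisation.
- For centres of 20 and 15 patients (assumed sizes) the chance is 0.48 and 0.59.

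**3. Overall arm sizes.** Under simple allocation the largest and smallest arms differ by 26 on average, and some arm has 228 or fewer with probability 0.53. The effect is negligible: a 228/252 pair gives 80.2–80.4% power, against 80.4% for 240/240.

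**4. Type I error and power.** Setting: one pairwise comparison, 216 evaluable per arm, 16 equal centres, a random centre intercept with an assumed SD on the log-odds scale, and 4,000 runs per cell. The simulation error of a power near 0.80 is √(0.8 × 0.2/4000) = 0.006. CMH is the Cochran–Mantel–Haenszel test stratified by centre.

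| Centre SD | Type I error, no strata, unadjusted | Power, no strata, unadjusted | Power, strata, unadjusted | Power, no strata, CMH | Power, strata, CMH |
|---|---|---|---|---|---|
| 0 | 0.054 | 0.80 | 0.80 | 0.79 | 0.80 |
| 0.5 | 0.051 | 0.80 | 0.80 | 0.80 | 0.82 |
| 1.0 | 0.048 | 0.79 | 0.81 | 0.84 | 0.85 |

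Strata plus CMH gain 0 to 6 points. At SD 1.0, adjustment alone brings most of the gain and strata alone about 2 points. At that SD, strata without adjustment also make the test conservative (type I error 0.03).

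**5. Adding GCS.** With stratification by centre and GCS band, and both carried into the test, simulated pairwise power rose from about 81% to 84–89% under assumed centre and GCS effects, a gain of 3 to 8 points. I checked this with low GCS in 40% of patients, a GCS log odds ratio of 1.0 to 1.4 and a centre SD of 0 to 1.0, all assumed. Power went from 0.80–0.82 to 0.83–0.87, inside the 0 to 8 point range.

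**The case against.** **The method may be stratified already.** A stratified permuted-block list is also a computer-generated sequence run by a central system, and block sizes are often kept out of an open-label protocol on purpose. A reader might infer one unstratified sequence, but the text neither says so nor rules it out. This stands, so the point is limited to what is not stated. It does not remove the point. The stratification factors, unlike the block sizes, are a design decision in force from the first patient. The primary test ignores centre in either case.

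**Differing skill is not documented.** A reader might infer that some operations are rarely done at some hospitals, or that surgeons differ in skill. The Study design section says that all surgeons were trained in all three techniques and that all three were routine at every centre. Residual differences between hospitals are plausible, but nothing in the documents shows them.

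**Chance imbalance is not confounding.** This stands. Type I error stays near 5%. For a factor held by 40% of patients, the 95% limit on the difference between two arms is 1.96 × √(2 × 0.4 × 0.6/240) = 8.8 points. If the factor raises the unfavourable rate by 30 points (both inputs assumed), the arm difference shifts by 0.088 × 0.30 = 2.6 points. That lies within the ordinary sampling error, 1.96 × √(0.387/216) = 8.3 points, where 0.387 = 0.33 × 0.67 + 0.21 × 0.79. The test already allows for it.

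**No within-centre comparison is planned, and the regression contains GCS.** Both are true. The within-centre ratios therefore describe how uneven the spread could be, and are not an error in the primary result. The regression is not the primary analysis, and it omits centre.

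**Conclusion.** The point holds as one of precision and specification. For a 16-hospital surgical trial, the Protocol states no balancing by centre or prognosis, and it fixes a primary test that uses neither. If the list is unstratified, about 3 of 16 equal centres would have a 2:1 or greater split between two operations. The cost is roughly 0 to 8 points of pairwise power from a base of about 80%. The upper end needs strong centre and GCS effects, for which the documents give no figures. The power figures also assume a pairwise comparison with 216 evaluable patients per arm.

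The documents do not support a claim of biased treatment comparisons, of a confirmed single unstratified list, or of unequal surgical skill. The departure from exactly 240 per group is immaterial. This is a cheap improvement and does not threaten the trial's validity.

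**What to change.** **Randomization section.** Specify the central allocation in one of two ways:
- stratified by centre with randomly varying block sizes; or
- minimisation with a random element on centre, GCS band and hematoma volume band. To balance prognosis as well as centre, this is preferable to many small centre-by-GCS strata.

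If the system already does one of these, one sentence naming the factors is enough; block sizes can stay undisclosed.

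**Statistical analysis section.** Carry the same factors into the primary comparison, for example with a stratified CMH test or an adjusted logistic regression. Step 4 shows that this brings most of the gain, and that stratifying without it makes the test conservative when centres differ strongly.

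**If allocation has already run without strata.** Say so, adjust the primary analysis for centre and preoperative GCS, and report the number of patients by arm and centre.

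**Cost.** Reconfiguring the existing central system and revising two sections, with no extra patients. Allocations become slightly easier to guess in an open-label trial, which varying block sizes or the random element limits. Small centres will leave some incomplete blocks.
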